#### Measures

Measures include the same background information, self-rate questions and self-evaluation scale of competence and the PBCT as used in Study 1. Additionally, Study 2 will include a self-evaluation of improvement in competence after the previous survey.

#### Procedure

Students will be invited to complete the REDCap survey approximately six months after attending the first lecture. Students may participate during a lecture or independently. Therapists in training access the survey independently through the survey link that is sent them by email approximately one year after responding to the first survey.

#### Analysis

The analyses will concentrate on within-group mean changes, utilizing person-centered analysis strategies to identify individual trajectories of change in competence. The same power analysis for Study 1 was used for Study 2, where a minimum sample size per group was determined to be 64 for a two-tailed t-test when the anticipated effect size (d) was set to 0.50, and the desired power level was set to 0.80. To anticipate drop-out during data collection, the sample size was set to 80 participants per group.

### Study 3

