The current research will progress in three subsequent sub-studies that build upon one another. The study aims to meet the following research goals in these three sub-studies:*The aim of Study 1* is to develop the PBCT and validate sensitivity to therapist experience. Research questions under Study 1 are: a) Does the PBCT show sensitivity to previous experience and training? b) Are therapists’ formal and informal training, work-related variables (e.g., work settings), and self-reported attributes related to competence and confidence associated with performance in the PBCT? This validation stage will be deemed successful if performance in the PBCT is associated with the level of training.*The aim of Study 2* is to continue the validation of the PBCT by ensuring responsiveness to further training. The second validation stage will be deemed successful if performance in the PBCT is improved after additional training for master’s students of psychology and psychotherapist trainees. In addition, the association between therapist characteristics and competence development are analyzed. Research questions under Study 2 are: a) Does the PBCT detect increases in competence during one year of psychotherapist training or brief psychology master’s program training? b) Are therapists’ formal and informal training, work-related variables (e.g., work settings), and self-reported attributes related to competence and confidence associated with performance in the PBCT?*The aim of Study 3* is to provide evidence of the importance of therapist competence for treatment outcomes in a brief intervention for enhancing mood and wellbeing delivered by novice therapists. In addition, competence development during brief training and intervention delivery is examined. Research questions under Study 3 are: a) Does the PBCT detect increases in novice therapists' competence after brief training or during the intervention? b) Is competence associated with the outcome of a brief intervention for mood problems provided by novice therapists? c) Can individual differences in the initial level of competence and changes in competence during training or delivery of the intervention be identified and modeled to improve training practices?

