#### Design and setting of the study

The psychotherapist trainees participating in Study 1 are invited to complete the PBCT and questionnaires after a follow-up period of one year to examine the sensitivity of the PBCT to further training and the development of competence during advanced training. In addition, the same psychology students participating in Study 1 are invited to complete again the PBCT and questionnaires after completing masters-level courses on clinical CBT to examine sensitivity to brief further training. Follow-up period for students is approximately six months. To account for the measurement effect, bachelor’s level psychology students not receiving additional training are recruited to complete the PBCT at two time points during three months.

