#### Participants

Participants (*N* = 240) are 1) master’s level psychology students participating to Study 1 (novice therapists; *n* = 80), 2) students in training to become CBT psychotherapists participating to Study 1 (therapist trainees; *n* = 80) and 3) bachelor’s level psychology students (control participants; *n* = 80).

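### The Study 2 success rule and stated analysis rest on within-group PBCT improvement and do not carry through the purpose of the untrained control group, so a pure retest gain could satisfy the rule

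*Protocol article*

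**What the plan says.** Three parts of the protocol article bear on this point.

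- **Success rule** (Research objectives and tasks, aim of Study 2): "The second validation stage will be deemed successful if performance in the PBCT is improved after additional training". The sentence goes on to name master's students of psychology and psychotherapist trainees. It names no comparator.
- **Analysis** (Study 2, Analysis): "The analyses will concentrate on within-group mean changes", with person-centred methods for individual trajectories. No between-group contrast of change is named. The sample size is carried over from Study 1: 64 per group for a two-tailed t-test at d = 0.50 and power 0.80, raised to 80 for drop-out.
- **Design** (Study 2, Design and setting; Participants): "To account for the measurement effect", bachelor's students "not receiving additional training are recruited to complete the PBCT at two time points during three months". They are listed as 80 control participants within N = 240.

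The retest intervals differ. For master's students, "Follow-up period for students is approximately six months"; trainees are retested "after a follow-up period of one year". The instrument does not change: Study 2 Measures specifies "the PBCT as used in Study 1".

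**The concern.** A person who takes the same video task twice may score higher the second time through familiarity alone. The design section recognises this and recruits a group to deal with it. The success rule and the stated analysis focus then leave that group out. If the untrained controls gained as much as the trained groups, the rule as published would still be met.

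Responsiveness to further training is one of the two validation properties sought for the PBCT, the other being sensitivity to prior training. A within-group change is the sum of any training effect and any retest effect, and a test on that sum cannot attribute it to training.

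**Working it through.** **1. The plan's own figure.** A two-sample t-test with d = 0.50, power 0.80 and two-sided alpha 0.05 (alpha is not stated; 0.05 is assumed) needs 63.8, so 64 per group. Power at 64 is 0.801. The stated figure reproduces. A paired test at a standardised mean change of 0.50 would need only 34. The stated 64 is thus a figure for comparing two independent groups. The step from 64 to 80 corresponds to 20% drop-out (1 − 64/80 = 0.20).

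**2. Inputs for the false-success calculation.**
- From the article: 64 completers per group (the stated minimum); improvement sought in two trained groups.
- Assumed: training effect zero; retest gain g of 0.1, 0.2 or 0.3 baseline SD; test-retest r of 0.6 to 0.8; equal SD at both occasions; the two groups independent; success in a group read as a significant increase on a paired two-sided 0.05 test. The article gives no g and no r, and it attaches no test to the success rule.

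**3. Formula.** The standardised mean change is dz = g / √(2(1 − r)). The chance of a significant increase is the upper tail of a noncentral t with 63 degrees of freedom and noncentrality dz × √64, beyond the critical value 1.998. Example with g = 0.2 and r = 0.6: dz = 0.2/√0.8 = 0.224, noncentrality 0.224 × 8 = 1.79, probability 0.42. For both groups, 0.421² = 0.18.

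**4. Results (n = 64 per group).**

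| Retest gain | One group, r = 0.6 / 0.7 / 0.8 | Both groups, r = 0.6 / 0.7 / 0.8 |
|---|---|---|
| 0.1 SD | 0.14 / 0.17 / 0.24 | 0.02 / 0.03 / 0.06 |
| 0.2 SD | 0.42 / 0.53 / 0.70 | 0.18 / 0.28 / 0.49 |
| 0.3 SD | 0.75 / 0.86 / 0.96 | 0.57 / 0.74 / 0.93 |

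With no retest gain the upward error rate is 0.025 per group, or 0.025² = 0.0006 for both. The rule names both trained groups, so the right-hand column is the chance of meeting it; the middle column is not.

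**5. The controlled contrast.** If the retest gain is the same in trained and control groups, comparing changes returns the upward error rate to 0.025 per trained group, whatever the size of the gain. For a training effect of 0.5 baseline SD and 64 per group, the two-sample effect on change scores is 0.5/√(2(1 − r)). Power is 0.80 at r = 0.5, 0.88 at 0.6, 0.95 at 0.7 and 0.99 at 0.8.

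**6. If the control gain is too large.** Suppose familiarity is stronger at three months than later, and subtracting the control change reduces a true 0.5 SD to a net 0.3 SD. Power at 64 per group then falls to 0.39 (r = 0.5), 0.47 (0.6), 0.59 (0.7) or 0.76 (0.8).

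**The case against.** The strongest reply is that the comparison is evidently intended. The controls are counted in the Study 2 sample, their purpose is stated, and the sample size is a two-group figure. To concentrate on within-group change does not exclude a controlled contrast, and a condensed article may leave the model to an analysis plan. This stands against a stronger reading that a reader might infer, namely that within-group change is the only analysis and the controls will go unused. The document does not say that. It does not remove the point, because the success rule is stated and names no comparator. A contrast added elsewhere would not be required for success under that rule.

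A second reply is that the rule carries no test or threshold, so the error rates depend on how one reads it. That is correct, and the rates are conditional on the reading given in the working.

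A third reply is that the retest gain may be small. The intervals are about six and twelve months, there are 24 simulations, and the automated feedback is described as based on the self-assessment and questionnaires rather than on PBCT answers. Each may limit the gain, and at 0.1 SD the joint rate is only 2-6%. Randomised video order deals with order within a sitting, not with familiarity at a second one. None of these features shows that the gain is zero, which an uncontrolled test has to assume.

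A fourth reply is that the controls are a poor match: bachelor's students, not randomised, retested within three months. This stands as a limit on the contrast and belongs in the fix.

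**Conclusion.** The point holds in this form: the published success rule and analysis focus do not carry through the stated purpose of the control group, and a retest gain alone could satisfy the rule. Under the assumptions in the working, the chance of that in both trained groups is about 2-6%, 18-49% and 57-93% for gains of 0.1, 0.2 and 0.3 SD. Per group it is 14-24%, 42-70% and 75-96%, against a nominal 2.5%. Both g and r are assumptions, so these figures show a range and do not predict what Study 2 will find. The structural fault does not depend on them, since the rule cannot separate retest from training at any size of gain.

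Two stronger readings are not supported. The per-group rates are not the chance of meeting the rule, because it covers both trained groups. Nor does the article leave retest unexamined across the project: Study 3 measures students twice before training to establish a baseline without training. That evidence does not enter the Study 2 rule, but it bears on how large a retest gain is likely to be. Sample size is not at fault.

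**What to change.** Restate the Study 2 success rule and primary analysis together, before the outcome data are analysed:

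- Success requires that mean PBCT change in master's students, and separately in trainees, exceeds mean change in the untrained controls, tested as a group-by-time contrast on change scores (two-sided 0.05 each). Change scores are preferable to baseline-adjusted analysis here because the groups are expected to differ at baseline.
- Report within-group change alongside, not as the criterion.
- State that the controls are non-randomised bachelor's students retested within three months, against about six and twelve months in the trained groups, so the contrast may over- or under-correct for retest.
- Use the Study 3 double baseline before training as supporting evidence on the size of the retest gain.

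The cost is wording. The planned 80 per group, controls included, is enough, and no new data are needed. There are two downsides to state openly. If controls gain on retest, the net effect will be smaller than the raw within-group change. If the three-month control gain exceeds the retest component in the trained groups, the contrast will lose power and could miss a real training effect.

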#### Analysis

The analysis strategy for Study 1 will focus on examining between-group differences, emphasizing mean differences and exploring associations between self-reported and tested competence and related professional qualities. Power analyses to determine appropriate sample sizes were calculated using an online tool available at https://www.danielsoper.com/statcalc/. For Study 1, a minimum sample size per group was determined to be 64 for a two-tailed t-test when the anticipated effect size (d) was set to 0.50, and the desired power level was set to 0.80. To anticipate drop-out during data collection, the sample size was set to 80 participants per group.

### Study 2

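### Study 2 plans a within-group analysis but takes its sample size from Study 1's two-group t-test, and it uses one drop-out margin twice for the same trainees and master's students

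*Protocol article*

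**What the plan says.** The Protocol article, Study 1, Analysis, sizes Study 1 for comparisons between groups: "The analysis strategy for Study 1 will focus on examining between-group differences". The minimum is 64 per group, "for a two-tailed t-test when the anticipated effect size (d) was set to 0.50", and "the desired power level was set to 0.80". It then adds a margin: "To anticipate drop-out during data collection, the sample size was set to 80 participants per group".

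Study 2, Analysis, names a different kind of analysis: "The analyses will concentrate on within-group mean changes". Its size is nevertheless carried over: "The same power analysis for Study 1 was used for Study 2, where a minimum sample size per group was determined to be 64". The same d, the same power and the same increase to 80 follow.

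Study 2, Design and setting of the study, shows who these people are: "The psychotherapist trainees participating in Study 1 are invited to complete the PBCT and questionnaires after a follow-up period of one year". The master's students of Study 1 are likewise invited again, after about six months. Study 2, Participants, lists each of these two groups at n = 80. The third group, 80 bachelor's-level students without further training, is not one of the three groups compared in Study 1. It is there so that the effect of repeated measurement can be allowed for.

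**The concern.** Two things do not fit together.

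First, a test of mean change within one group uses the SD of the change, and its power depends on the number of pairs and the correlation between the two occasions. A test between two independent groups depends on neither. A sample size derived for one cannot be quoted with its power for the other unless the result is shown to carry over.

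Second, the 80 recruited for Study 1 are meant to shrink to 64. Study 2 starts from the same people, counts them as 80 again, and again allows for shrinkage to 64. The 16 spare participants per group can be lost only once.

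Responsiveness to training is the second of the two validation stages of the process-based competence task (PBCT). A reader of the article would take 64 completers and power 0.80 as its planning basis, and neither figure follows from the design described.

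**Working it through.** **Inputs.** From Study 2, Analysis: d = 0.50, two-tailed t-test, power 0.80, minimum 64 per group, 80 recruited. Assumed: two-sided alpha 0.05, which is not stated but reproduces 64. Assumed: a pre-post correlation r from 0 to 0.7, since none is given. The article does not say whether d is in raw-SD units or in units of the SD of change (dz). Powers are from the noncentral t distribution.

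**1. The plan's own figure.** For two independent groups of n, the noncentrality is d × √(n/2) with 2(n − 1) degrees of freedom. Solving for power 0.80 at d = 0.50 gives n = 63.77, rounded up to 64. At n = 64 the noncentrality is 0.50 × √32 = 2.83 and power is 0.801. So 64 reproduces exactly, as a two-group figure.

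**2. The analysis that Study 2 names.** For a paired test the noncentrality is dz × √n with n − 1 degrees of freedom. At dz = 0.50:

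| Pairs | Noncentrality | Power |
|---|---|---|
| 34 | 0.50 × √34 = 2.92 | 0.81 |
| 51 | 0.50 × √51 = 3.57 | 0.94 |
| 64 | 0.50 × √64 = 4.00 | 0.98 |

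The exact solution for power 0.80 is 33.37, so 34 pairs suffice.

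**3. If d = 0.50 is in raw-SD units.** Then dz = d / √(2(1 − r)):

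| r | dz | Pairs for 0.80 | Power at 64 | Power at 51 |
|---|---|---|---|---|
| 0 | 0.354 | 65 | 0.795 | 0.70 |
| 0.2 | 0.395 | 53 | 0.88 | 0.79 |
| 0.3 | 0.423 | 46 | 0.91 | 0.84 |
| 0.5 | 0.500 | 34 | 0.98 | 0.94 |
| 0.7 | 0.645 | 21 | 0.999 | 0.995 |

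A figure near 64 suits a paired test only if repeat scores are almost uncorrelated.

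**4. The drop-out margin.** The implied loss is 1 − 64/80 = 20%. Lost once, 80 × 0.80 = 64. Lost again at follow-up, 64 × 0.80 = 51.2, or about 51. Reaching 64 at follow-up then requires no follow-up loss at all, or 64 / (0.80 × 0.80) = 100 at the start. With a follow-up loss of 10% or 30% from 64, about 58 or 45 remain, and paired power at dz = 0.50 is 0.96 or 0.91. With 51 pairs, the detectable dz at power 0.80 is 0.40.

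**5. If change is compared between a trained group and the controls.** The noncentrality is d × √(n₁n₂/(n₁ + n₂)), with d = 0.50 in change-score units:

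| Trained v control | Noncentrality | Power |
|---|---|---|
| 64 v 64 | 0.50 × √32 = 2.83 | 0.80 |
| 51 v 64 | 0.50 × √(3264/115) = 2.66 | 0.75 |
| 51 v 51 | 0.50 × √25.5 = 2.52 | 0.71 |

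If d is instead in raw-SD units, 51 v 64 gives 0.61 at r = 0.3, 0.75 at r = 0.5 and 0.93 at r = 0.7.

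**The case against.** The strongest reply is that the error is mostly on the safe side. Within-group change is the only mean comparison that Study 2, Analysis, names, and the Research objectives section defines success as better performance after training. For that test 64 pairs are more than enough at dz = 0.50, and 51 pairs still give 0.94. If both trained groups must improve, 0.938² = 0.88 (independent groups). This stands, and it limits the point.

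A reader might infer that Study 2 is underpowered, citing 0.71 to 0.75. The document does not support that. Those powers belong to a comparison of change with the bachelor's controls, and the article neither specifies such a test nor makes it the success criterion. The stated purpose of the controls makes it a natural use of them, so its power is worth reporting if it is intended. It cannot be presented as the power of the stated analysis.

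A reader might also take 51 as the number to expect. No drop-out rate is stated. The 20% is inferred from 80 and 64, and 51 requires that loss in full at both stages, the first of them a single-occasion online survey. The Discussion lists measures against attrition: automatic reminders, feedback to participants and embedding in courses. But it also singles out the one-year follow-up as the place where retention is a worry, so assuming no follow-up loss is hard to defend.

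Condensation does not excuse the point. The article prints a size, a test, an effect size and a power for Study 2, and they disagree with its own analysis and recruitment text.

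**Conclusion.** The point holds as a mismatch in the stated justification, not as a demonstrated shortage of power. The 64 and 0.80 are right for two independent groups and wrong for the within-group analysis, where 34 pairs reach 0.80 and 64 reach 0.98 at dz = 0.50. The margin from 64 to 80 is counted twice for two of the three Study 2 groups; the bachelor's controls are a separate sample.

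Under an assumed 20% loss at each stage, about 51 remain. The within-group test then falls below 0.80 only if d = 0.50 is in raw-SD units and the pre-post correlation is no higher than about 0.2. All figures assume two-sided alpha 0.05.

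**What to change.** Rewrite the sample-size part of Study 2, Analysis:

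- Give the paired calculation, and say whether d = 0.50 is in raw-SD or change-SD units. If raw, state the assumed pre-post correlation.
- For the trainees and master's students, start from the expected Study 1 completers (64 on the plan's own margin), apply a separate, stated follow-up loss, and report the resulting power or detectable difference. With 20% again, that is 51 pairs: power 0.94 at dz = 0.50, detectable dz 0.40.
- If change is to be compared between a trained group and the bachelor's controls, say so and give that power: 0.80 for 64 v 64, and about 0.75 (51 v 64) or 0.71 (51 v 51) at d = 0.50 in change-score units, conditional on the double loss.

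The cost is one reworded paragraph. No added enrolment is needed.

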#### Design and setting of the study

Master’s level psychology students will receive a brief training on process-based CBT training, after which they deliver a short intervention to clients. Master’s level psychology students receive three days of training on a) building a functional case conceptualization to identify individual treatment targets, and b) using process-based CBT processes of therapeutic change. The training and provision of interventions are built in the mandatory studies offered to students completing a master’s degree in psychology. This novel training and related interventions serve as one of several modes of study for the students. Weekly supervision and peer-supervision are included in the curriculum for this mode of study on the course.

Second, the students will deliver the six-session intervention to two client participants. Interventions will be delivered in three waves. Students will receive weekly supervision from clinical psychologists and psychotherapist and attend weekly peer-supervision.

#### Participants

Participants are master’s level psychology students (*n* = 70) and voluntary individuals (*N* = 140) who seek support for common psychological problems (e.g., low mood, anxiety, psychological distress).

The inclusion criteria for client participants are: 1) willingness to participate in an intervention aimed at increasing psychological wellbeing that is delivered by a psychology student, 2) having experienced one or several common problems of psychological wellbeing, i.e., stress, low mood or anxiety related problems, 3) willingness and ability to participate in a study that requires visits to the Psychotherapy Teaching and Research Clinic at JYU and responding to online surveys. The exclusion criteria will be: 1) severe psychological ill-being that requires assessment and treatment by a mental health professional, 2) psychological symptoms that significantly affect daily functioning, 3) ongoing psychological treatment or psychotherapy, 4) changes in medication prescribed for psychological symptoms during past 4 months, 5) alcohol or drug addiction, 6) self-injurious behaviors, or 7) current suicidal thoughts.

